### Statistical analysis

Pain will be the primary endpoint and will be determined using a VAS, an algometer, the FIQ, and the McPQ. Quality of life as assessed by SF-36, salivary serotonin level, and overall parameters of pain will be secondary endpoints. Statistical analysis will be performed using IBM SPSS software (version 13.0; IBM, Armonk, NY, USA), and a two-sided *P* value <0.05 will be considered significant. The intragroup and intergroup comparisons will be carried out with two-way repeated-measures analysis of variance with post hoc Bonferroni correction or the Kruskal-Wallis test with a post hoc Dunn test. The choice of tests will be based on the distribution (normal or non-normal) of the data by the Shapiro–Wilk test. For categorical data, χ^2^ statistics will be used.

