**Methods/Design:**

A randomized controlled clinical trial will be conducted. It will involve 60 women ≥ 35 years of age with a diagnosis of FM and TMD. After recruitment, patients will be randomly allocated to one of four groups: a control group (no intervention), a group that will receive a phototherapy intervention (PHO), a group that will be prescribed muscle-stretching, aerobic, and facial exercises (EXT), or a group that will receive phototherapy plus exercise interventions (PHO + EXT). The trial will last 10 weeks, and the following outcomes will be evaluated on two separate occasions (baseline and within 24 h after the last day of the protocol). Pain intensity will be analyzed using a visual analogue scale and the McGill Pain Questionnaire, and pain thresholds will be punctuated using a digital algometer. FM symptoms will be assessed using the Fibromyalgia Impact Questionnaire, and quality of life will be determined with the 36-item Short Form Health Survey. Serotonin levels will be evaluated in salivary samples using a competitive enzyme-linked immunosorbent assay.

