## Background

Fibromyalgia (FM) is a chronic syndrome characterized mainly by pain, nonrestorative sleep, fatigue, morning stiffness, depression, and cognitive disorders [1, 2]. Patients with FM often show widespread pain in the presence of tender points (expressed as mild or greater tenderness), which provide the most sensitive, specific, and accurate criteria for making the diagnosis [1, 3]. Using this classification, almost all patients with FM are women because they have more tender points than do men [4]. Overall, FM symptoms lead to significant reduction in functional capacity and quality of life [2, 5, 6]. Developing treatment teams is useful, including clinicians with expertise in patient education, exercise training interventions, and cognitive behavioral therapy [7–9]. An optimized treatment can be provided using the following steps: (1) overall recommendation (e.g., patient education), (2) nonpharmacologic (e.g., exercise, cognitive behavioral therapy, alternative medicine, and central nervous system neurostimulatory intervention), and (3) pharmacologic (e.g., tricyclic complexes, gabapentinoids, γ-hydroxybutyrate, naltrexone, cannabinoids, selective serotonin reuptake antagonists, nonsteroidal anti-inflammatory drugs, and opioids) [4].

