### Population and sample size

In a literature review, we found that FM prevalence is higher in women between ages 35 and 60 years than in men [21]. All women patients aged ≥ 35 years and referred for FM and TMD diagnostic evaluation were eligible for inclusion in the present trial. Patient eligibility comprises an evaluation of medical history, physical examination, and dental and rheumatologic routine evaluations. Moreover, patients had to have undergone FM screening as reported by the American College of Rheumatology using the Fibromyalgia Impact Questionnaire (FIQ) 1. The TMD diagnosis had to be reported on the basis of TMD research diagnostic criteria (axes I and II) [22]. The sample size calculation was based on a previous study by Consalter et al. [23] in which the TMD prevalence was 80 % in patients with FM. A 95 % reliability and a 10 % error rate was assumed to estimate the sample size (n) as follows [24]:$$ n={\left(\frac{z_{a/2}\sqrt{p\left(1-p\right)}}{\varepsilon}\right)}^2={\left(\frac{1.96\ast \sqrt{0.8\ast 0.2}}{0.1}\right)}^2 $$

A total of 60 women will be randomized for this trial, with 20 women allocated per group.

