#### Fibromyalgia symptoms and quality of life

Outcome parameters will be evaluated with the FIQ. The FIQ is a multidimensional instrument developed to assess several FM symptoms (pain, fatigue, stiffness, tenderness, sleep disorders, depressed mood, anxiousness, problems with memory, imbalance, sensitivity to non-painful stimuli, and performing daily tasks) [29]. The Medical Outcomes Study 36-item Short Form Health Survey (SF-36) will also be used [29].

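### The Fibromyalgia Impact Questionnaire counts towards the primary endpoint, pain, although the protocol itself describes it as a multidimensional symptom instrument

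*Protocol article*

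**What the plan says.** The Statistical analysis section ranks the endpoints. On the primary one it says: "Pain will be the primary endpoint and will be determined using a VAS, an algometer, the FIQ, and the McPQ". It names no FIQ subscale or item and does not say how results on the four instruments lead to one conclusion about pain. Its secondary endpoints are quality of life by SF-36, salivary serotonin, and the overall parameters of pain. The FIQ is not among them.

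Two other places describe what the FIQ measures:

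- The outcome section on fibromyalgia symptoms and quality of life: "The FIQ is a multidimensional instrument developed to assess several FM symptoms". Eleven symptoms follow, with pain the first.
- The abstract: "Pain intensity will be analyzed using a visual analogue scale and the McGill Pain Questionnaire", with the algometer used for pain thresholds. The FIQ comes in a separate sentence: "FM symptoms will be assessed using the Fibromyalgia Impact Questionnaire".

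The FIQ also appears at entry. The section on population and sample size refers to "FM screening as reported by the American College of Rheumatology using the Fibromyalgia Impact Questionnaire (FIQ".

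**The concern.** The objective and the hypothesis concern chronic pain. A primary endpoint called pain should respond when pain changes and should not respond when only something else does. An instrument that spans sleep, mood, memory and daily function does not have that property unless its use is limited to the pain content.

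The difficulty is practical here. The Background reports that training programmes in fibromyalgia reduce fatigue, depression and anxiety as well as pain. In the two exercise arms the FIQ could therefore improve partly or wholly through symptoms other than pain, and the plan as written would place that result under primary pain. Conversely, an effect confined to pain could be weakened by averaging with symptoms that did not move.

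This is a question of what is being measured. Splitting the significance level across the four instruments would not answer it.

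**Working it through.** The plan gives no figure on this point that could be reproduced. The check is a count and a comparison of statements.

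**Step 1: count the listed FIQ content** (section on fibromyalgia symptoms and quality of life).

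- Pain itself: 1.
- Arguably pain-related: tenderness, and sensitivity to non-painful stimuli: 2.
- Other: fatigue, stiffness, sleep, low mood, anxiety, memory, balance, daily tasks: 8.
- Total: 1 + 2 + 8 = 11.

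Share that is pain, narrow reading: 1/11 = 9%. Share on the widest reading: 3/11 = 27%. Not pain on either reading: 8/11 = 73%. These are shares of the listed symptoms. They are not scoring weights, which the article does not give.

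**Step 2: compare the role of each instrument.**

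| Instrument | Abstract | Statistical analysis |
|---|---|---|
| Visual analogue scale | pain intensity | primary, pain |
| McGill Pain Questionnaire | pain intensity | primary, pain |
| Algometer | pain thresholds | primary, pain |
| FIQ | fibromyalgia symptoms | primary, pain |

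Three of the four instruments are described consistently. Only the FIQ changes from a symptom measure to a pain measure.

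**Step 3: compare with the secondary list.** The overall parameters of pain are secondary. According to their own section they include sleep quality, stiffness and morning fatigue, together with direct pain data such as daily duration of pain and the number of days with high pain. Sleep, stiffness and fatigue are also on the FIQ list. The same symptoms are thus secondary in one place and part of primary pain in another, and some direct pain data rank below a mixed instrument.

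**Step 4: follow the plan as written.** Suppose that fatigue, sleep and mood improve in an exercise arm and pain does not. An FIQ score that includes those symptoms improves, and the Statistical analysis section classes the result as primary pain. Nothing in the article prevents this.

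**Step 5: the entry wording.** The Background says of tender points, "which provide the most sensitive, specific, and accurate criteria for making the diagnosis". The recruitment section gives the fibromyalgia diagnosis to a rheumatologist using previously defined criteria. The population section speaks of screening with the FIQ. The three statements do not fit together smoothly, but the recruitment section shows that the FIQ is not the only basis for entry.

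**The case against.** The best defence is that a journal article condenses the protocol. It mentions no FIQ total and no scoring, and the full plan may use only the pain item, which the Statistical analysis wording would allow. This part stands: the overall score is the natural reading of an unrestricted reference, but it is not stated. It does not remove the point, because the article is not silent on the role of the FIQ. It states that role in two ways that conflict.

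A second defence is that pain goes together with sleep disturbance, fatigue, mood and memory problems, as the Discussion says. Association does not make these symptoms pain, and the Discussion itself names them separately.

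A third is that one instrument may not be enough to claim success. This is correct and limits the conclusion. If all four instruments, or one named pain measure, had to improve, a change in the FIQ alone could not carry the claim. The article gives no rule either way.

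A reader might also infer more than the text supports:

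- *That women are admitted by symptom burden and not by diagnosis.* The recruitment section requires a rheumatologist's diagnosis and at least five years since diagnosis, and the population section adds history, physical examination and rheumatologic evaluation.
- *That regression to the mean contaminates the change within groups.* This needs selection on an FIQ score and reuse of that score as baseline. The article states neither a cut-off nor such reuse.
- *That a percentage can be put on the distortion.* This would need domain weights and baseline scores, and neither is given.
- *That the abstract or the outcome section already ranks the FIQ as secondary.* They describe its content only. The Statistical analysis section alone ranks endpoints.

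**Conclusion.** The point holds as a contradiction in the definition of the primary endpoint. The article counts an instrument as pain although, by its own description, at least 8 of the 11 symptoms listed for it are not pain. The consequence is a risk in both directions: changes in other symptoms could be reported as a primary pain benefit, and a real pain effect could be diluted.

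The conclusion rests on two assumptions: that the unrestricted reference means an overall FIQ score, and that a result on the FIQ can contribute to the claim about pain. The documents do not support saying that pain will be declared improved on the FIQ alone.

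It should be corrected, since it affects what the trial can conclude about its main question. The entry wording is a minor matter of consistency.

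**What to change.** In the Statistical analysis section, do one of the following by dated amendment before any unblinded analysis (the Trial status section says that allocation is already under way):

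1. Move the FIQ overall score to the secondary endpoints, labelled as fibromyalgia symptoms and impact. This matches the content given in the abstract and the outcome section.
2. Keep an FIQ element under pain, but state that only its pain item counts there, with the overall score secondary.

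As a minor edit, reconcile the population section's statement on FIQ screening with the Background and the recruitment section, so that the part played by the FIQ at entry is clear.

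No new data are needed. Under the first option the primary heading has three instruments in place of four. Either change corrects what is measured. How the remaining instruments are combined, and how error is controlled across them, is a separate matter that it does not settle.

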#### Visual analogue scale

We will use a visual analogue scale (VAS) to assess pain level. The VAS consists of a limited strip of 10 cm in length. This strip has at its ends the anchor terms *no pain* and *worst pain possible*. The patient will be instructed to report the level of pain sensation to a point along this line, with the scores ranging from 0 to 10 and obtained by measuring the distance between the end anchored by the term *without pain* and the point marked by the participant [29]. Additional analysis will include changes from randomization to the end of withdrawal (week 10) in an adapted Portuguese version of the McGill Pain Questionnaire (McPQ) [30].

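### Four instruments share primary status at two-sided 0.05, with no rule on which one decides success and no correction across them

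*Protocol article*

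**What the plan says.** The protocol article ranks its endpoints only in the section Statistical analysis: "Pain will be the primary endpoint and will be determined using a VAS, an algometer, the FIQ, and the McPQ". Quality of life (SF-36), salivary serotonin and the overall pain parameters are secondary. The same section sets one general criterion, "a two-sided *P* value <0.05 will be considered significant", and names the tests: "two-way repeated-measures analysis of variance with post hoc Bonferroni correction or the Kruskal-Wallis test with a post hoc Dunn test".

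Three other places bear on the point:

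- The section Visual analogue scale describes the VAS and then brings in the McGill Pain Questionnaire (McPQ) with the words "Additional analysis will include changes from randomization to the end of withdrawal (week 10".
- The section Fibromyalgia symptoms and quality of life says: "The FIQ is a multidimensional instrument developed to assess several FM symptoms". Its list has eleven entries. Pain comes first, and fatigue, sleep, mood, memory and daily tasks are among the others.
- The Discussion again calls pain the main endpoint, without saying which measure represents it.

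No section names a lead instrument, a composite, an order of testing, a division of alpha, or the number of instruments that must be significant.

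**The concern.** A primary endpoint should tell the reader, before the data are seen, which result answers the trial's question. Here pain is a concept measured four ways, and each measure can produce its own p-value at 0.05. The Bonferroni and Dunn procedures follow the ANOVA or Kruskal-Wallis test of a given outcome. They protect comparisons among groups or time points within that outcome and leave the error across the four outcomes uncontrolled.

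Two things are at stake. First, one favourable result out of four could be presented as the primary result, and the choice could be made after the results are known. Second, the FIQ total reflects several symptoms, so a change driven by mood or fatigue could be reported as a primary effect on pain.

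**Working it through.** **Inputs from the article**

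- Primary instruments: 4 (VAS, algometer, FIQ, McPQ), from Statistical analysis.
- Threshold: 0.05, two-sided, the same for every test.
- Correction across instruments: none stated.
- Groups: four, from the Abstract.
- Group size: Population and sample size says "A total of 60 women will be randomized for this trial, with 20 women allocated per group". Four groups of 20 make 80, and 60/4 = 15, so both 15 and 20 per group were tried.

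**Inputs that are assumptions**

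- Significance on any one instrument counts as success. The article states no rule.
- Every pair of instruments has the same correlation, varied from 0 to 0.9. The article gives no correlations.
- For the F tests, the group-by-time effect decides. With two time points this is a one-way comparison of change scores across the four groups.

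**The plan's own figures.** The article gives no familywise error rate to reproduce. Its only error figure is the 0.05 threshold per test. The sample-size formula does not point to a lead instrument either: (1.96 × √(0.8 × 0.2) / 0.1)² = 61.5, close to the 60 planned, and the only outcome in it is the prevalence of TMD. No pain measure enters.

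**Independent instruments.** P(at least one false positive) = 1 − (1 − 0.05)⁴ = 1 − 0.8145 = 18.5%. The upper bound under any dependence is 4 × 0.05 = 20%.

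**Correlated instruments.** These figures were simulated with no true effect on any instrument. The z tests used 1,000,000 runs (simulation error about 0.04 percentage points). The four-group F tests used 100,000 runs (about 0.1 points).

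| Assumed correlation | Four z tests at 0.05 | Four F tests at 0.05, 15 per group | Four F tests at 0.05, 20 per group | Four z tests at 0.0125 |
|---|---|---|---|---|
| 0 | 18.6% | 18.3% | 18.5% | 4.9% |
| 0.3 | 17.4% | 17.7% | 17.6% | 4.7% |
| 0.5 | 15.5% | 16.2% | 16.2% | 4.3% |
| 0.7 | 13.1% | 13.7% | 13.7% | 3.6% |
| 0.8 | 11.4% | 11.9% | 12.1% | 3.2% |
| 0.9 | 9.4% | 9.7% | 9.8% | 2.6% |

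The F tests, which are closer to the planned ANOVA, agree with the z tests to within about 0.7 points. The group-size discrepancy makes no material difference.

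**With Bonferroni across instruments.** 0.05/4 = 0.0125 each, and 1 − (1 − 0.0125)⁴ = 4.9% if independent. The last column shows lower values as correlation rises.

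**The opposite rule.** If all four instruments had to be significant at 0.05, the z-test simulation gives 0.6% at correlation 0.7 and 1.9% at 0.9.

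**The case against.** The strongest reply is that the article nowhere says that one significant instrument is enough. Saying that pain is determined with four instruments could equally mean that all must agree or that the pattern is judged as a whole, and under an all-four rule the error is well below 5%. This stands. A reader might infer that the trial's false-positive rate simply is 13% to 19%, but the documents do not support that as a fact. It needs the any-one rule and correlations no higher than about 0.7. What the text does establish is that the rule is missing.

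Four other stronger readings also go too far:

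- That there is no multiplicity correction at all. There is one, within each instrument. What is missing is correction across the four.
- That the article contradicts itself on the McPQ. The wording in the VAS section can mean in addition to the VAS. The only section that ranks endpoints puts the McPQ among the primary measures and not among the secondary ones. The wording is ambiguous, no more.
- That the FIQ is not a pain measure. Its list begins with pain and includes tenderness. The fair statement is that its total is not specific to pain, and the article does not say whether the total or the pain content will be used.
- That separate tests at each algometer point push the error higher still. The article names no summary over points, but it does not say that points will be tested one by one, and such detail is commonly left to the full protocol or analysis plan.

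It can also be said that an analysis plan not shown may name a lead measure. That does not remove the point. The protocol itself gives four instruments primary status and sets the threshold, so its text would still need to be brought into line.

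**Conclusion.** The point holds as a defect in how the primary endpoint is fixed: four instruments, one 0.05 threshold, no decision rule and no control of error across instruments. Its size depends on the rule that is eventually applied. If any one instrument suffices, the familywise error is 18.5% under independence and falls to about 9% at a correlation of 0.9. Even at that high correlation it is nearly twice 5%. The any-one rule and the correlations are assumptions; the number of instruments, the threshold and the within-instrument scope of the Bonferroni and Dunn steps come from the article. The FIQ's breadth and the McPQ wording are lesser matters of alignment. Because the defect affects the trial's main inference, it should be settled before unblinding.

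**What to change.** Amend the Statistical analysis section in one of two ways.

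1. Name one primary instrument, tested at two-sided 0.05, and move the other three to secondary. Change in VAS pain is a natural choice because it measures pain directly, but it is not the only defensible one.
2. Keep all four as primary and apply Holm or Bonferroni across them. Under Bonferroni each is tested at 0.0125, and the familywise error is at most 4.9% in the calculation above.

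Under either option, reduce algometry to one pre-stated summary, such as the mean threshold over all prescribed points. State whether the FIQ total or its pain content is analysed, and align the McPQ wording in the VAS section with the ranking in Statistical analysis.

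No new data, visits or patients are needed. It is still more than an edit: the Trial status section says that allocation is under way, and the trial is registered and ethics-approved, so the change must be a dated amendment made before unblinding. The cost is that three measures lose primary status under the first option, or that each is held to a stricter threshold, with some loss of power, under the second.

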### Interventions

The trial will be 10 weeks long, during which time patients will undergo two sets of phototherapy, exercise, or placebo procedures per week. Phototherapy will be applied 30 min before each exercise bout, and treatment sessions will be carried out Tuesdays and Thursdays each week. For eligible patients, the research will record outcome parameters at baseline prior randomization and 48 h after the last day of intervention. This evaluator will be blinded to the allocation of the patients into the respective groups.

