### Outcome parameters

The outcome parameters described below will be evaluated at baseline and 24 h after the last day of the experimental protocol.

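### The between-arm comparison is placed in a baseline/post-treatment repeated-measures ANOVA with no contrast fixed; a baseline-adjusted post-treatment difference would be at least as efficient as any reading of it

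*Protocol article*

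**What the plan says.** Statistical analysis puts the within-arm and between-arm comparisons of continuous outcomes into one model: "The intragroup and intergroup comparisons will be carried out with two-way repeated-measures analysis of variance with post hoc Bonferroni correction". The alternative for non-normal data is "or the Kruskal-Wallis test with a post hoc Dunn test". The significance rule is "a two-sided *P* value <0.05 will be considered significant". No model term or contrast is named as the treatment effect.

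The design around that sentence is simple. In the abstract, "patients will be randomly allocated to one of four groups", and "the following outcomes will be evaluated on two separate occasions". Interventions places the first measurement before randomisation: "the research will record outcome parameters at baseline prior randomization and 48 h after the last day of intervention". Outcome parameters gives the second measurement as 24 h after the end instead of 48 h. That difference needs reconciling, but it does not affect this point, because either way there is one baseline and one post-treatment value.

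Change from randomisation is mentioned for the McGill questionnaire (under Visual analogue scale, as an additional analysis) and for salivary serotonin. It is not mentioned for the VAS score itself, algometry or the FIQ, which are also listed as measures of the primary pain endpoint.

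**The concern.** In a group-by-time ANOVA with two occasions, the group factor compares arm means averaged over baseline and post-treatment. Baseline is taken before randomisation, so arms do not differ there in expectation, and averaging it in dilutes the treatment effect. The other ways to compare arms in the same model are the group-by-time term, which compares changes, and arm contrasts at the post-treatment visit alone. These estimate the full effect, but neither makes the best use of the baseline. The change score subtracts all of it, however weakly it predicts the later value. The post-treatment contrast ignores it.

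With 15 to 20 women per arm and six pairwise comparisons, this choice matters. A real benefit could be missed, or reported at half its size under the worst reading, while within-arm improvements from the same model look positive.

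**Working it through.** **The plan's own figure.** The article's sample-size formula gives n = (1.96 × √(0.8 × 0.2) / 0.1)² = 61.5, close to the stated 60. It is a precision calculation for a prevalence. It contains no pain effect, SD, correlation or power, so it gives nothing to compare with the powers below.

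**Inputs from the article.** Four arms, two occasions, baseline before randomisation, two-sided 0.05, Bonferroni. On numbers it says "A total of 60 women will be randomized for this trial, with 20 women allocated per group". Four arms of 20 make 80, and 60/4 = 15, so both 15 and 20 per arm are shown.

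**Assumptions, not in the article.** True post-treatment difference between two arms d = 1 SD; equal SD at both visits; baseline/post-treatment correlation r = 0.3 to 0.7; Bonferroni over all six pairs of four arms, so α = 0.05/6 = 0.0083.

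**Expected estimate under each reading**
- Group factor, pooled over time: (0 + d)/2 = d/2
- Post-treatment only: d
- Change (group × time): d − 0 = d
- Baseline-adjusted (ANCOVA): d

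A simulation of the four-arm design (20,000 runs, r = 0.5) gave 0.50 for the first and 1.00 for post-treatment only and for change. On the VAS, a true 2-point advantage would be estimated as 1 point under the first reading and 2 points under the others.

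**Standardised effect (estimate divided by per-woman SD), d = 1, r = 0.5**
- Group factor: 0.5/√((1 + r)/2) = 0.5/√0.75 = 0.577
- Post-treatment only: 1/1 = 1.000
- Change: 1/√(2(1 − r)) = 1/√1 = 1.000
- Baseline-adjusted: 1/√(1 − r²) = 1/√0.75 = 1.155

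**Power for one pair.** Noncentral t with noncentrality (standardised effect) × √(n/2) and 4(n − 1) degrees of freedom: 56 for n = 15, 76 for n = 20. The degree of freedom spent on the covariate changes the adjusted figures by less than 0.1 percentage point.

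| n per arm | α | r | Group factor | Post only | Change | Adjusted |
|---|---|---|---|---|---|---|
| 15 | 0.0083 | 0.3 | 16% | 51% | 35% | 56% |
| 15 | 0.0083 | 0.5 | 13% | 51% | 51% | 66% |
| 15 | 0.0083 | 0.7 | 12% | 51% | 78% | 86% |
| 20 | 0.0083 | 0.5 | 20% | 67% | 67% | 82% |
| 15 | 0.05 | 0.5 | 34% | 77% | 77% | 87% |
| 20 | 0.05 | 0.5 | 44% | 88% | 88% | 95% |

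**Why the adjusted contrast is never materially worse.** Its variance relative to post-treatment only is 1 − r². Relative to change it is (1 − r²)/(2(1 − r)) = (1 + r)/2. Neither ratio exceeds 1 for r between 0 and 1. At r = 0.5 both are 0.75, so 15 women per arm with adjustment match 15/0.75 = 20 per arm without it. At r = 0 the adjusted and post-treatment-only contrasts coincide apart from one degree of freedom.

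**The case against.** A reader might infer that the plan assigns the between-arm test to the group main effect, so that the trial as written will report half the true benefit. The article does not support this, because it names no term. A two-way model contains the interaction by construction. Before-after tests within an arm cannot come from the time main effect, which pools arms, so at least those post hoc tests must be made within cells. The parallel reading of the between-arm test is arms compared at one visit. The mentions of change for the McGill questionnaire and serotonin also point away from averaging baseline in. All of this stands, so the halving is conditional.

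Three further objections have weight. First, comparing arms after treatment alone is valid in a randomised trial, and for r below 0.5 it beats the change contrast (51% against 35% at r = 0.3). This is right, and it is why the recommendation is adjustment and not change scores. Second, naming the contrast is detail that a condensed article may leave to a fuller document. That is fair, so its absence alone would not be a point. What remains is that the article does choose the method, and a better one is available at no cost. Third, the argument covers only the ANOVA branch; it does not carry over in this form to Kruskal-Wallis with Dunn.

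**Conclusion.** The point holds as an improvement to the stated analysis, not as a demonstrated error. Every reading of the ANOVA is matched or beaten by the baseline-adjusted post-treatment difference. With d = 1 SD, 15 per arm, six-pair Bonferroni and r = 0.5, adjustment raises power from 51% to 66% against either unbiased reading. The gain over post-treatment only grows with r (5 points at r = 0.3, 35 at r = 0.7), while the gain over change shrinks (21 points at r = 0.3, about 7 at r = 0.7).

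The large loss, 13% power and a halved estimate, arises only if group means pooled over time are used, which the text neither states nor excludes. The halving does not depend on r. The power figures rest on assumed d and r. At r = 0 the group factor has the same power as the change contrast (48% each at α = 0.05, n = 15), although its estimate is still halved.

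**What to change.** For the ANOVA branch, amend Statistical analysis to say three things. The between-arm result for each continuous outcome is the post-treatment difference between arms, adjusted for that outcome's baseline value (ANCOVA). The Bonferroni correction applies to those adjusted contrasts. No conclusion about treatment is drawn from the group main effect or from group means pooled over time.

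This costs a few sentences. The baseline is already collected for every outcome, the named software fits the model, and no extra patients or visits are needed. If a fuller analysis plan exists, it should carry the same wording.

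### A normality pre-test chooses between repeated-measures ANOVA and Kruskal-Wallis; the fallback is wrong for paired intragroup comparisons and undefined between groups, and neither branch uses baseline as efficiently as ANCOVA

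*Protocol article*

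**What the plan says.** Under Statistical analysis, the protocol article assigns within-arm and between-arm comparisons alike to one of two methods: "two-way repeated-measures analysis of variance with post hoc Bonferroni correction or the Kruskal-Wallis test with a post hoc Dunn test". The rule for choosing is: "The choice of tests will be based on the distribution (normal or non-normal) of the data by the Shapiro–Wilk test". The significance rule is that "a two-sided *P* value <0.05 will be considered significant".

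The rule reaches the primary endpoint, which has four instruments: "Pain will be the primary endpoint and will be determined using a VAS, an algometer, the FIQ, and the McPQ". The Abstract gives four arms ("patients will be randomly allocated to one of four groups"). Under Outcome parameters, the measures "will be evaluated at baseline and 24 h after the last day of the experimental protocol", so each woman contributes two values per measure.

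The section names no paired rank test and no baseline covariate. It does not say whether Shapiro-Wilk is applied to raw values, changes or residuals, or which variable Kruskal-Wallis would rank. Change from randomization is mentioned only for the McGill questionnaire, as an additional analysis (Visual analogue scale section), and for serotonin (Salivary serotonin section).

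**The concern.** The two branches are presented as substitutes, but they are not interchangeable.

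- **Intragroup.** A before-after comparison within one arm is paired. Kruskal-Wallis with Dunn treats one woman's two readings as coming from two women. The correlation that makes the paired design efficient is discarded, and the nominal 5% level no longer applies.
- **Intergroup.** With two time points, the group-by-time interaction is a comparison of mean change. Kruskal-Wallis on end values compares end levels without baseline. Unless the ranked variable is fixed, a normality test on the trial's own data may decide which quantity is compared, separately for each of the four primary pain measures.
- **Baseline.** Even where the branches agree on the question, neither uses the baseline as efficiently as a covariate-adjusted analysis. That matters with four small arms.
- **Intragroup p-values.** Even when correctly computed, a before-after p-value in one arm does not measure a treatment effect.

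**Working it through.** **Inputs from the protocol article.** Four arms, two measurements per woman, two-sided alpha 0.05. The Population and sample size section gives both 60 women in total and 20 per group. With four arms, 60/4 = 15 per group, whereas 4 × 20 = 80 in total, so both 15 and 20 are used below. The article states no power, effect size, SD or before-after correlation for these analyses, so there is no figure of its own to reproduce on this point.

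**Assumptions, not in the document.** Normal data with unit SD; correlation r = 0.3, 0.5 or 0.7; effects as stated in each step. Results are simulated. Repeat runs agree to within about three percentage points.

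**1. Kruskal-Wallis on before-after values in one arm.** Treating the values as independent takes the variance of the mean difference as 2σ²/n. The true variance is 2σ²(1 − r)/n. In large samples, the nominal 1.96 cut-off therefore acts like 1.96/√(1 − r): 2.34, 2.77 and 3.58 at r = 0.3, 0.5 and 0.7. The test must be conservative, and increasingly so as r rises. Simulated at 15 per group:

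- Size: about 2%, 1% and 0.1 to 0.2% at r = 0.3, 0.5 and 0.7, instead of 5%.
- Power for a 0.8 SD change at r = 0.5: about 56%, against 82% for a paired t-test.

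**2. Efficiency of the between-group options.** Variance of a group contrast relative to end values alone (= 1): change 2(1 − r); ANCOVA 1 − r².

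| r | End value | Change (ANOVA interaction) | ANCOVA |
|---|---|---|---|
| 0.3 | 1 | 1.4 | 0.91 |
| 0.5 | 1 | 1.0 | 0.75 |
| 0.7 | 1 | 0.6 | 0.51 |

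ANCOVA has the smallest variance in every row. At r = 0.5, ANCOVA on 60 women is worth a change-score analysis on 60 × 1.0/0.75 = 80.

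**3. Power of the global four-group test**, assumed true effects 0/0.5/0.5/1.0 SD, for r = 0.3/0.5/0.7:

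| Analysis | 15 per group | 20 per group |
|---|---|---|
| ANCOVA | 63/71/88% | 77/87/95% |
| Group-by-time interaction | 45/59/84% | 59/74/92% |
| Kruskal-Wallis, end values | 54/55/55% | 71/71/70% |

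Kruskal-Wallis on change scores stays close to the interaction: about 55% against 59% at r = 0.5 and 15 per group. The ranking of the two branches depends on r when end values are ranked: at 15 per group, Kruskal-Wallis leads at 0.3 (54% against 45%) and trails badly at 0.7 (55% against 84%).

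**4. How often chance could switch the branch.** If Shapiro-Wilk were applied at 0.05 to each of the 4 × 2 = 8 group-by-time cells (the article does not say), exactly normal data would give at least one rejection in about 1 − 0.95⁸ = 34% of trials.

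**5. Intragroup p-values.** Assume every arm improves by 0.5 SD with no difference between arms, and use uncorrected paired t-tests. At least one active arm is significant while control is not in about 47/46/34% of trials at 15 per group and 46/40/21% at 20 per group (r = 0.3/0.5/0.7).

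**The case against.** Several stronger readings are tempting, and the document does not support them.

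- **That Kruskal-Wallis cannot address group-by-time at all.** Run on individual change scores, it is a rank analogue of the interaction with little loss of power. The article does not exclude this, and a condensed article may leave the ranked variable to the full plan. On that reading both between-group branches ask essentially the same question. This stands as a limit on the point. It does not rescue the intragroup comparison, which the text also assigns to Kruskal-Wallis.
- **That the fallback produces false positives.** It does not. Within an arm it is conservative. Between randomised groups it holds its size at about 4 to 5%, on end values or on change.
- **That the primary branch is invalid.** The ANOVA interaction uses the baseline and is unbiased under randomisation. ANCOVA is a gain in efficiency over it, not the repair of a bias.
- **That intragroup results will be read as evidence of efficacy.** The article lists both comparisons in one sentence and sets no hierarchy or decision rule. The 21 to 47% describes a risk if such a claim were made, and a Bonferroni correction would change it.
- **That the analyst has a free choice.** The selection rule is stated in advance, and the Randomization, blinding, and experimental groups section says the analyst is blinded to allocation. The weakness is that chance features of the data trigger the switch, not that someone who knows the arms could steer it.

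**Conclusion.** The point holds in this form. The text assigns a paired comparison to an independent-samples test, with a size of about 1% instead of 5% and power of about 56% instead of 82% in the middle scenario. It also makes the between-group method depend on a normality pre-test without saying what the fallback ranks. Both branches have lower power than baseline-adjusted ANCOVA at every correlation and both group sizes tried. The gap to the interaction runs from about 3 points (r = 0.7, 20 per group) to 18 points (r = 0.3, at either group size). The gap to Kruskal-Wallis on end values runs from about 6 points (r = 0.3, 20 per group) to 33 points (r = 0.7, 15 per group).

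All sizes and powers rest on assumed normal data, correlations and effects, none of which the article gives. The mismatch between test and paired data, and the ordering of the variances, do not depend on the chosen effect sizes. The consequence is lost power and an estimand that is not firmly fixed, rather than inflated false-positive rates.

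**What to change.** Replace the Shapiro-Wilk switch with one pre-specified primary analysis for each continuous outcome: ANCOVA of the end-of-trial value on group, adjusted for the baseline value of the same measure, reporting between-group differences with 95% confidence intervals. Support it with a sensitivity analysis of the same contrast by rank ANCOVA, permutation or bootstrap, so that non-normality does not change the question.

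Report intragroup changes descriptively. If an intragroup rank test is kept, name a paired one such as Wilcoxon signed-rank. If Kruskal-Wallis is kept between groups, state that it is applied to change scores.

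The cost is a change of wording in the statistical section. No new data or visits are needed. The Trial status section says allocation is still under way, so the change should be made and dated before the outcome data are analysed.
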